### Measures

#### Lifestyle behaviors

Physical activity will be assessed with an accelerometer (ActiGraph wGT3X+ or wGT3X-BT), as well as with the International Physical Activity Questionnaire (IPAQ)-short form. Accelerometers capture overall body movement, intensity of activity, and time. Participants will wear small (pager-sized) blinded accelerometers (i.e., participants cannot see the values) just above their right hipbone for 7 days to assess typical physical activity in all forms (e.g., light, moderate, and vigorous activity). To be valid, the accelerometer should be worn a minimum of 10 hours per day [34] and for 5 days [35]. All participants will be given a self-addressed pre-paid envelope to return the accelerometer to the study staff after they have worn it for 7 days. For remote data collection at month 3, the device will be mailed to the participant, and a pre-paid envelope will be provided to mail back to study staff. For month 6, the accelerometer will be mailed 1 week before the visit, and the participant will be asked to return it at their in-person month 6 visit. The IPAQ assesses walking for exercise, walking for transportation, moderate and vigorous physical activity, and time spent sitting. It is widely used to measure physical activity and has shown good test-retest reliability (Spearman’s rho clustered 0.8 for all versions) and fair criterion validity (median rho = 0.30) [36]. Diet behaviors, including fruit and vegetable consumption and fat intake, will be assessed with a web-based tool, the Diet History Questionnaire-III [37]

#### Quality of life

The 12-item short form health survey (SF-12) is a widely used QoL measure producing two summary scores: physical component score and mental component score. The SF-12 has adequate validity and reliability and is positively associated with wellbeing [38].

#### Blood markers (survivors only)

Four inflammatory markers will be assessed using blood samples at baseline and month 6, as they are associated with PC patients’ mortality [39, 40]: C-reactive protein (CRP), tumor necrosis factor alpha (TNF-alpha), interferon gamma (IFN-gamma), and interleukin 4 (IL-4). CRP is selected because it is a global marker of inflammation and is predictive of chronic conditions, including cardiovascular disease [41]. TNF-alpha similarly indicates a systemic inflammatory state. IFN-gamma is chosen because it increases when there is a type I immune response (i.e., cell mediated or inflammatory), whereas IL-4 increases when there is a type II immune response (i.e., humoral or anti-inflammatory).

#### Anthropometric measures

At baseline and month 6, weight and height (to calculate body mass index), waist and hip circumference, and % of body fat will be assessed from research staff. Height (cm) will be measured without their shoes with a stadiometer, and weight (kg) and % body fat will be assessed with Tanita Body Fat Analyzer (TBF-300A). Waist and hip circumference (in) will be assessed with Myotape. Each of them will be measured twice. At month 3, self-reported weight and height will be collected.

#### Self-efficacy

Self-efficacy for exercise and healthy eating will be assessed with a total of 32 items [42]. Participants will use a 5-point Likert scale, from 1 (*I know I cannot*) to 5 (*I know I can*), to rate their level of confidence in being physically active (12 items) and reducing calories and fats (25 items). Both the exercise (*α* ≥ .83) and healthy eating items (*α* ≥ .85) have good internal consistencies.

#### Social support

Social support will be measured using items from the Social Support and Exercise Survey developed by Sallis to assess social support from family and friends [43] and later modified by Eyler [44] for use with racially/ethnically diverse populations. The items in the modified version will assess both emotional (three items, *α* = .77) and informational (three items, *α* = .71) social support using a 5-point Likert scale to measure participants’ agreement or disagreement from 1 (*strongly disagree*) to 5 (*strongly agree*).

#### Perceived stress

The Perceived Stress Scale [45] assesses the degree to which respondents find their lives to be stressful. This scale has been widely used in various cultures and countries for measuring psychological stress and has established acceptable psychometric properties.

#### Anxiety

Participants’ state anxiety will be assessed using the 6-item State Anxiety Scale [46]. The 6-item version has acceptable reliability and validity, producing similar scores to those obtained using the original version.

#### Uncertainty

Illness uncertainty will be measured using six items adapted from the Mishel Uncertainty in Illness Scale (MUIS) [47], which assesses survivors’ perceptions of uncertainty about their disease using a 5-point Likert scale from 1 (*strongly disagree*) to 5 (*strongly agree*). Also, we will use another six items adapted from the Assessment of Survivor Concerns (ASC) [48], whose convergent and discriminant validity was supported. Each item is asked to respond using a 4-point Likert scale from 1 (*not at all*) to 7 (*very much*). Partners will answer about their uncertainty regarding their partners’ PCa.

#### Dyadic adjustment

A 7-item version of the Dyadic Adjustment Scale (DAS-7), which assesses level of agreement on topics (e.g., philosophy of life, aims/goals/beliefs, and amount of time spent together), frequency of time together (e.g., working together on a project), and happiness, will be measured. The DAS-7 has a good internal consistency (Cronbach’s alpha ranged from .75 to .80) and demonstrated its discriminant and concurrent validity [49].

#### Communication

Communication about cancer will be assessed using items adapted from the Couple’s Illness Communication Scale (CICS) [50]. The CICS comprises four items for survivors (e.g., “It is hard for me to express feelings about my illness to my partner”) and partners (e.g., “It is hard for me to express feelings about his/her illness to my partner”) each. Participants are asked to respond using a 5-point Likert scale from 1 (*disagree strongly*) to 5 (*agree strongly*). We will modify “illness” to “prostate cancer.” The CICS has good internal consistency (.84 for patients and .80 for partners) and adequate test-retest reliability over a 3-month period (.71 for patients and .75 for partners).

#### Analytic plans

The intervention adherence rate for each dyad is defined as the proportion of intervention sessions completed by both the survivor and partner. We will look at percentage of both survivor and partner completing a minimum of 9 out of 12 coaching calls and both nutrition counseling sessions. Feasibility of recruitment will be achieved if ≥ 30% of eligible participants enroll in the study, and ≥ 80% participants complete follow-up assessments at months 3 and 6. Feasibility of intervention adherence will be achieved if average proportion of intervention adherence rate is ≥ 0.7 (e.g., coaching calls and nutrition sessions completed by both the survivor and partner ≥ 70%).

Linear mixed models will be used when combined data from both survivors and partners are analyzed due to their correlation within couples. The primary endpoint for the efficacy of the interventions is the differences between intervention and control group in outcome changes between baseline and 6 months post baseline. Specifically, an intervention indicator will be included and tested for the difference of increase in outcomes between groups. In our data, cluster corresponds to couples and random intercepts will be used to represent the pair effects. We will also conduct analysis of covariance to compare efficacy outcomes of interest pre and post intervention between intervention and control group separately for survivors and partners. Covariates and corresponding baseline outcome will be adjusted for in the analyses. Two-sided statistical tests will be performed, and the significance level for each test will be set at 0.05 without adjustment for multiple testing. All results from the statistical tests will be interpreted as hypothesis generating rather than conclusive findings. We will additionally perform various descriptive analyses, including dyadic analyses, to characterize the sample and compare participants and those who refused/withdrew on demographic and medical factors.

A process evaluation of the intervention will be conducted using in-depth interviews at each assessment time point with a subsample of the survivor-partner dyads (up to *n* = 15 dyads from the intervention arm and up to *n* = 5 dyads from the control arm). Questions will address participants’ experiences; thoughts about strengths, weaknesses, and needed improvements; perceptions about outcomes and impact; and overall reactions to and satisfaction with the intervention. Control arm dyads are also included in the interviews to understand their experiences and behavior changes over the study time period. This approach will assist us identifying elements of the intervention that were successful and/or need improvement for the larger trial. All interviews will last no longer than 2 h and will be audio-taped and transcribed verbatim. Transcripts will be entered into NVivo and analyzed using thematic data analysis procedures [51]. Two individuals will independently code the data for all transcripts to minimize potential biases.

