All participants will be assessed at three time points: baseline, month 3, and month 6. Eligible dyads will attend an in-person baseline visit at MD Anderson. At this visit, study staff and research assistants will describe study procedures, complete consent forms, and collect baseline data. PCa survivors’ blood will be collected as well. Approximately a week later, the dyads in the intervention arm will receive an exercise prescription from an exercise physiologist and nutrition counseling from a registered dietitian in-person or via telephone. At month 3, the dyads will complete self-administered questionnaires at home, and blood will not be collected. At month 6, the dyads will visit MD Anderson and complete self-administered questionnaires. Blood draw again will be conducted among PCa survivors. Self-administered questionnaires will be completed either online (via RedCap) or on paper. For in-person data collection at baseline and month 6, survivors will receive a $25 gift card per visit, and partners will receive a $20 gift card per visit. For month 3, survivors and partners will receive a $15 gift card each. Participants will be anticipated to be enrolled in the study in July 2019.

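### Both stated efficacy analyses use only baseline and month 6; for outcomes also measured at month 3, a repeated-measures model would use those data and need a weaker assumption about dropout.

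*Protocol article*

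**What the plan says.** Under Analytic plans, the efficacy endpoint is "the differences between intervention and control group in outcome changes between baseline and 6 months post baseline". Two methods are named:

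- **Mixed model.** Its stated purpose is the survivor-partner correlation: "Linear mixed models will be used when combined data from both survivors and partners are analyzed due to their correlation within couples". Its structure is that "cluster corresponds to couples and random intercepts will be used to represent the pair effects". The test is on an intervention indicator. No visit term, arm-by-visit term or person-level effect is described.
- **ANCOVA.** The plan is an "analysis of covariance to compare efficacy outcomes of interest pre and post intervention between intervention and control group separately for survivors and partners", adjusted for baseline.

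In that section month 3 appears only in the retention criterion (at least 80% completing months 3 and 6).

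The data collection is wider than the analysis. Under Recruitment and data collection procedures, "All participants will be assessed at three time points: baseline, month 3, and month 6". The same section adds: "At month 3, the dyads will complete self-administered questionnaires at home, and blood will not be collected". Under Lifestyle behaviors, the accelerometer is repeated: "For remote data collection at month 3, the device will be mailed to the participant". Blood markers are taken at baseline and month 6 only. At month 3, measured anthropometry is replaced by self-reported weight and height.

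**The concern.** Physical activity, a named secondary-aim outcome, has an objective month 3 measurement with no stated use in the efficacy analysis. A change score or pre/post ANCOVA has no outcome for someone without month 6 unless a further step is added, even when that person's month 3 data are complete.

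Three features make this more than a formality:

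- Up to 20% loss counts as success.
- When one member of a dyad withdraws, the other is asked to withdraw too, so losses come in pairs.
- The arms carry very different burdens: 12 coaching calls of 45 to 60 minutes, two dietitian sessions and self-monitoring, against a list of websites. Reasons for leaving could therefore differ by arm.

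If intervention participants who are doing poorly at month 3 leave more often, those who remain look better than the arm as a whole. The pilot is meant to support an application for a larger trial, so an inflated preliminary effect would carry forward.

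**Working it through.** **1. The plan's own figures.** The article gives no effect size, SD, between-visit correlation or power for efficacy, so there is no efficacy figure to reproduce. Its feasibility figures under Sample Size Justification do reproduce:

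- P(at least 40 consents of 50) = 0.880 at a consent rate of 85% and 0.262 at 75% (stated: 88% and 26%).
- 1.96/√30 = 0.358 and 1.96/√20 = 0.438 (stated: 0.36 SD and 0.44 SD).

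**2. Scale of the efficacy comparison** (one person per dyad, unadjusted, SD = 1).

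- All observed: 1.96 × √(1/30 + 1/10) = 0.72 SD half width; power for a 0.5 SD effect is 28%.
- After 20% loss, 30 × 0.8 = 24 and 10 × 0.8 = 8: 1.96 × √(1/24 + 1/8) = 0.80 SD; power is 23%.

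**3. Bias from dropout.** All inputs here except the 20% are assumptions. Large-sample simulation of survivors, 400,000 per arm, SD 1:

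- Correlation between any two visits: 0.5 or 0.7.
- True effect: 0.25 SD at month 3 and 0.5 SD at month 6.
- Missing month 6: 20% in each arm, with logit P(missing) = a − b × (month 3 value − arm mean). The slope b is set by arm, and a is solved to give 20%.
- Estimator A: ANCOVA of month 6 on arm and baseline, completers only.
- Estimator B: as A, but missing month 6 values are predicted within arm from baseline and month 3. This stands in for a likelihood analysis that includes month 3.

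Bias in the month 6 effect (SD), when month 3 is observed for all:

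| Dropout | A, corr 0.5 | A, corr 0.7 | B, either |
|---|---|---|---|
| Completely at random | 0.00 | 0.00 | 0.00 |
| b = 1 in both arms | 0.00 | 0.00 | 0.00 |
| b = 1, intervention only | +0.04 | +0.04 | 0.00 |
| b = 2, intervention only | +0.07 | +0.06 | 0.00 |
| b = 1 intervention, −1 control | +0.09 | +0.08 | 0.00 |

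**4. Other assumptions.** With correlations of 0.6 (baseline to month 3), 0.55 (baseline to month 6) and 0.7 (month 3 to month 6), and intervention-only dependence, the large-sample bias was +0.037 at b = 0.5, about +0.06 at b = 1.0 and about +0.09 near b = 1.5 (odds ratio e^1.5 ≈ 4.5 per SD). A simulation at 30 versus 10 over slopes of 0.5 to 1.5 gave about +0.03 to +0.12. So 0.12 is the outer end; the large-sample runs stop near 0.09.

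**5. Month 3 also missing.** If half of those missing month 6 also lack month 3, estimator B corrects only part of the bias (correlation 0.5):

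- b = 1, intervention only: +0.044 falls to +0.019, so (0.044 − 0.019)/0.044 = 57% is removed.
- Opposite slopes: +0.091 falls to +0.041, so 55% is removed.

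**6. Precision.** In 4,000 simulated trials of 30 versus 10, the empirical SE was 0.348 without month 3 and 0.338 with it: (0.348 − 0.338)/0.348 = 2.9%.

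**The case against.** The strongest reply is that the article states no rule for missing data, that articles commonly leave this to the full protocol or analysis plan, and that a baseline-adjusted comparison at the end of the intervention is a standard choice. Naming a month 6 contrast does not in itself bar month 3 values from a model or an imputation.

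That reply disposes of three stronger readings that a reader might infer:

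- *That anyone without month 6 is excluded.* The article does not say so. It supports only the narrower statement that such a person has no outcome value in the analyses as described.
- *That dropout bias will be present.* This is conditional. No document shows that people who do not improve tend to leave, and the bias vanishes under random dropout or equal dependence in both arms.
- *That every outcome could be analysed at month 3.* The article does not list the month 3 questionnaires. Inflammation, a named secondary-aim outcome, has no month 3 value, and measured anthropometry has no comparable one.

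It is also fair that efficacy is secondary, that the tests are declared hypothesis generating, and that participants are to be compared with those who refused or withdrew.

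What survives is the model structure. The article does more than stay silent: it fixes a two-time-point endpoint and states that "random intercepts will be used to represent the pair effects", with nothing at person level. Adding month 3 rows to that model would leave the correlation between a person's two visits unmodelled, so the structure itself needs a change.

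**Conclusion.** The point holds as a cheap improvement, not as an error that threatens the trial. As described, both efficacy analyses ignore month 3 data that are collected anyway. The bias those data could reduce is zero under random or equal-in-both-arms dropout. It is roughly 0.03 to 0.12 SD when dropout depends on the month 3 response in the intervention arm only, at log-odds slopes of 0.5 to 1.5 per SD, with about 20% missing and the correlations assumed above. Its sign supposes that poor responders leave; it reverses if good responders do.

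Even 0.12 SD is only 0.12/0.80 = 15% of the 95% half width after 20% loss. Month 3 data remove the bias where month 3 is observed, and only a little over half of it where half the dropouts also miss month 3. They do not cure dropout that depends on the unseen month 6 value. The primary feasibility aim is unaffected.

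**What to change.** For outcomes measured the same way at months 3 and 6, fit one linear mixed model to both follow-ups:

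- **Fixed effects:** baseline value, visit, arm, arm-by-visit, baseline-by-visit, role (survivor or partner) and recruitment site.
- **Random intercepts:** couple, and person within couple.
- **Efficacy estimate:** the arm contrast at month 6, so the endpoint is unchanged.

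For survivors and partners separately, use the same model, without the role term, and with a person intercept only. Keep ANCOVA for blood markers and measured anthropometry. State which questionnaires are repeated at month 3, so that it is clear which outcomes fall under which analysis.

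Cost: wording only, with no new data or visits. The model is slightly larger and assumes data missing at random given baseline and month 3. The precision gain is only about 3%, so the reason to change is the weaker dropout assumption. Results stay hypothesis generating.

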### Sample Size Justification

Our sample size of 40 dyads provides adequate statistical support to help evaluate our primary aim of feasibility. In terms of evaluating feasibility based on recruitment, if the true consent rate of eligible dyads is 85%, then there will be 88% probability for us to screen 50 couples or less to arrive at 40 couples that consent; if the true consent rate is 75%, then there will be only 26% probability for us to screen 50 couples or less to arrive at 40 couples consenting. With the chosen total study sample size of 40 dyads, the randomization ratio would then be determined by the sample size chosen specifically for the intervention arm. With a lack of data available in the literature on the adherence of the proposed intervention among racial/ethnic minority PCa patients and partners, it would be valuable to allocate more patients to the intervention arm than the control arm to allow a more accurate assessment of the intervention adherence rate (as part of the primary objective of the study).

Specifically, when the sample size is 30, a two-sided 95% confidence interval (CI) for the average adherence rate will extend 0.36 standard deviation (SD) from the observed average rate, where SD is the estimated standard deviation of the adherence rate, assuming the CI is based on the large sample z statistic. This is in contrast to the corresponding half width of the 95% CI for the average adherence rate of 0.44 SD when the number of dyads in the intervention arm is 20 (as a result of a 1:1 randomization ratio), representing a less precise estimate of the mean adherence rate. Finally, we would like to keep a control arm with a reasonable number of patients (10 as chosen) to allow assessment of preliminary efficacy of the intervention with a reasonable level of accuracy, yet as a secondary objective of the study.

## Discussion

To our knowledge, Watchful Living will be the first dyadic lifestyle intervention conducted among AA and Hispanic men on AS and their partners. Strengths of this study will include (1) use of a mixed-methods research design, (2) application of the systematic intervention adaptation process, (3) assessment of inflammatory markers, and (4) use of an objective measure of physical activity. If effective, the intervention may have a higher health impact compared with a typical lifestyle intervention targeting only survivors (or partners), as survivors’ morbidity/mortality might be reduced (tertiary prevention), and partners’ own susceptibility to cancer may be decreased (primary prevention).

Recruiting cancer survivors is challenging, and recruiting couples will be an additional challenge. Given that numerous barriers have been reported with regard to participating in cancer research by underrepresented populations [52] and participating in health research by racial/ethnic minorities [53], various recruitment strategies (both passive and active) will be required. In particular, building strong team works with multiple hospitals and multidisciplinary teams including investigators who work with racial/ethnic minority cancer survivors and family members may be a key to succeed. We expect that results from this study will inform helpful strategies for recruitment and intervention with racial/ethnic minority PCa cancer survivors on AS and their partners. Lessons learned from this study will be used to further refine the intervention and apply for a large-scale grant.

## Data Availability

The datasets generated and/or analyzed during the current study are not publicly available due to confidentiality but may be available from the corresponding author on reasonable request.

## Abbreviations

PCa: Prostate cancer
AA: African American
NHW: Non-Hispanic White
QoL: Quality of life
AS: Active surveillance
PSA: Prostate-specific antigen
SF-12: 12-item short form health survey
CRP: C-reactive protein
TNF-alpha: Tumor necrosis factor alpha
IFN-gamma: Interferon gamma
IL-4: Interleukin 4
MUIS: Mishel Uncertainty in Illness Scale
ASC: Assessment of Survivor Concerns
DAS-7: Dyadic Adjustment Scale
CICS: The Couple’s Illness Communication Scale
CI: Confidence interval
SD: Standard deviation
